### Work package 5: health economic analysis and methodological development (months 24–48)

The overall research question for this WP5 is ‘What are the costs and benefits associated with investing in initiatives that facilitate relationships between traditional healers and the formal healthcare systems to improve access to care for those with SMDs?’ We will conduct primary data collection and analysis specific to the intervention developed in WP3. Our analyses will allow us to (a) generalise our work to interventions that aim to improve access more broadly, which will increase their impact and value to decision-makers; and (b) inform the development of mental health economics in LMICs and help address the need for capacity-building in this field.

### Capacity-building activities

We will identify capacity needs and co-develop and deliver high-quality capacity-building activities in Bangladesh and Nigeria, ranging from modules on research methodology to doctoral-level training and courses aimed at healthcare and leadership.

#### Doctoral research theses

The TRANSFORM programme is supporting three PhD candidates at the University of Warwick – one from Bangladesh and two from Nigeria – who will carry out their primary research activities in their home countries. These students, who were selected after a competitive process, commenced their doctoral studies in April 2022. The PhD topics include projects that are nested within TRANSFORM and stand-alone projects that are closely aligned to the TRANSFORM research priorities. At least two supervisors at the University of Warwick and one supervisor in the partner country are allocated to each student for their PhDs.

### Analysis plan

#### Qualitative analysis

For WP1, the collected transcribed data (both images and text) will be subjected to thematic analysis using qualitative software (NVivo 20). Analysis will be conducted first independently and then collaboratively to ensure reliability and validity within each site. The analysis will identify understandings and experiences of mental illness, poverty and daily life in the selected communities, as well as help-seeking for mental illness and practices of healers and health workers. The findings will inform the planning of the training interventions for CHWs and traditional/faith healers so that the interventions are contextually relevant and include the views of people with lived experience of mental illness and their families, healers and health professionals.

Findings from WP1 will also inform the qualitative evaluation of process and outcome after the intervention using the Qualitative Impact Protocol (QuIP).^36^ The QuIP is a method for qualitative impact evaluation for community-led and community-delivered interventions. It focuses on credible impact evaluation in relation to seeking to attribute outcomes to a specific intervention using interpretive methods. The QuIP uses a contribution analysis approach, combining quantitative monitoring of key indicators with qualitative, self-reported attribution of impact to provide sufficient evidence to test the theory of change behind the activity being evaluated.^37^ Importantly, although the QuIP evaluation can be designed by the study team, independent researchers, who are not associated with the intervention, will undertake the interviews to avoid confirmation bias and strengthen replicability.

The data collection for the process evaluation will include a replication of elements from the WP1 ethnographic assessment, including interviews with key participants on the referral pathway and group and individual interviews using participatory techniques. These will include people who accessed biomedical care and those who did not. In addition, interviews will be conducted with some of the previously interviewed natural groups when the listing and ranking and help-seeking matrix are repeated to assess whether there have been any changes in understanding. Data will be subjected to thematic analyses and these findings will inform the contextual interpretation of our quantitative findings.

#### Quantitative evaluation

In WP4, we will adopt a two-fold approach. Primarily, we will assess the impact of the proposed intervention on the (mental health) care pathway of individuals with SMDs and its potential effect on their health status. We will assess impact on the referral pathway by comparing referral rates made to the participating healers 12 months before and after intervention (training) is delivered. We will undertake a pre–post regression analysis to quantify the referral difference at the healer level after adjusting for healers’ and patients’ characteristics. Both the crude and the adjusted rate change and its corresponding 95% confidence interval will be provided.^38^ The change in referral rate will be the primary outcome of interest for this study.

We acknowledge that some participants may be directed to biomedical services by a healer but, for various reasons, may not actually access biomedical care. To further evaluate the impact of a healer's referral, we will try our best to trace their referrals and find out whether potential participants used mental health clinics.

In addition to the primary outcome, a number of patient-related secondary outcomes will be analysed. At this (patient) level, analysis will focus on clinical outcomes, functioning, participant and family satisfaction, medication adherence and attendance for clinical follow-up (Table 1 outlines the measures and time points for assessments).Uptake of healthcare will be evaluated longitudinally: at baseline (i.e. intake) and at months 1, 2 and 3. Similarly, clinical outcomes will be assessed longitudinally using the Global Assessment of Symptoms (GAS), Global Assessment of Functioning (GAF) and clinician-rated primary and secondary diagnoses. Carer burden will be assessed at baseline and post-intervention at month 3 using the Perceived Family Burden Scale (PFBS), and family satisfaction will be assess longitudinally using the Verona Service Satisfaction Scale (adapted to LMIC contexts). We will investigate service utilisation and associated costs using the abbreviated version of the Client Services Receipt Inventory (CSRI) – modified as used in our previous study.^39^ We will employ a linear mixed model to estimate longitudinal changes, adjusting for patient characteristics, time and baseline values/scores. Estimates and effect sizes will be reported, together with their 95% confidence intervals.

**Table 1 tab01:** Primary and secondary outcomes to be collected and their corresponding time points

		Assessment time point							
Domain	Tool	Pre-intervention	Baseline/intake	Month 1	Month 2	Month 3	Post-intervention	Analysis plan	Estimates reported
Number of individuals from study sites accessing biomedical care	Review of health record systems at NIMH in Dhaka (Bangladesh) and Ibadan (Nigeria)	✓					✓	Pre–post analysis	Referral rate and 95% CI
Number of referrals made by CHWs and traditional and faith healers	For each referral, CHWs will record date of referral and referral source (e.g. self, family member, faith or traditional healer)						✓	Pre–post analysis	Referral rate and 95% CI
Pathways to care (number and type of help-seeking contacts made prior to accessing biomedical care, and duration of untreated illness)	Nottingham Onset Schedule (NOS)		✓				✓	Pre–post analysis	Referral rate and 95% CI
Clinical characteristics of individuals accessing biomedical care	See assessment below	✓					✓	Longitudinal	Mean change since baseline
Sociodemographic profile									
	Age	✓	✓				✓	Longitudinal	Mean change since baseline
	Gender	✓	✓				✓	longitudinal	Mean change since baseline
	Education level		✓					Baseline only	descriptive only
	Religious background	✓	✓				✓	Longitudinal	Mean change since baseline
	Employment status		✓					Baseline only	Descriptive only
	Socioeconomic status		✓					Baseline only	descriptive only
	Family and marital status		✓					Baseline only	Descriptive only
	Area of residence	✓					✓	Longitudinal	Mean change
	Number of children <18 years old	✓	✓					Pre-intervention/baseline only	Descriptive only
Symptom severity	Global Assessment of Symptoms (GAS)		✓	✓	✓	✓		Longitudinal (baseline, months 1, 2 and 3)	Mean change (repeated measures)
Clinical/symptom profile	Clinician-rated primary and secondary diagnoses as recorded in charts		✓					Baseline only	Descriptive only
Level of functioning	Global Assessment of Functioning (GAF)		✓	✓	✓	✓		longitudinal (baseline, months 1, 2 and 3)	Mean change (repeated measures)
Physical health	Body mass index (BMI)		✓			✓		Longitudinal (baseline, month 3)	Mean change (repeated measures)
Carer burden	Perceived Family Burden Scale (PFBS)		✓			✓		Month 3 only	Descriptive only
Engagement with services	Record each month of whether patient contacted treatment provider and type of contact (phone, in-person, etc.).			✓	✓	✓		Longitudinal (months 1, 2 and 3)	Rate change (repeated measures)
Service utilisation and costs	Abbreviated version of modified version of Client Services Receipt Inventory (CSRI)		✓			✓		Longitudinal (baseline, month 3)	Mean/rate change (repeated measures)
Medication adherence	Medication Adherence Rating Scale (MARS)			✓	✓	✓		Longitudinal (months 1, 2 and 3)	mean change (repeated measures)
Patient and family satisfaction with services	Verona Service Satisfaction Scale (adapted to LMIC contexts)			✓	✓	✓		Longitudinal (months 1, 2 and 3)	Mean change (repeated measures)
Quality of life	EuroQoL five dimensions questionnaire (EQ-5D)		✓			✓		Longitudinal (baseline, month 3)	Mean change (repeated measures)

CHW, community health worker; NIMH, National Institute of Mental Health; LMIC, low- and middle-income country.

We will follow checklists such as the STROBE Statement to report our observational research. We are intending to develop a dedicated statistical analysis plan (SAP) with detailed description of the analyses undertaken (primary and sensitivity), the handling of missing values and model-assumption violations. The alpha = 0.05 significance level will be used in all analyses.

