## Abstract

This paper introduces the TRANSFORM project, which aims to improve access to mental health services for people with serious and enduring mental disorders (SMDs – psychotic disorders and severe mood disorders, often with co-occurring substance misuse) living in urban slums in Dhaka (Bangladesh) and Ibadan (Nigeria). People living in slum communities have high rates of SMDs, limited access to mental health services and conditions of chronic hardship. Help is commonly sought from faith-based and traditional healers, but people with SMDs require medical treatment, support and follow-up. This multicentre, international mental health mixed-methods research project will (a) conduct community-based ethnographic assessment using participatory methods to explore community understandings of SMDs and help-seeking; (b) explore the role of traditional and faith-based healing for SMDs, from the perspectives of people with SMDs, caregivers, community members, healers, community health workers (CHWs) and health professionals; (c) co-design, with CHWs and healers, training packages for screening, early detection and referral to mental health services; and (d) implement and evaluate the training packages for clinical and cost-effectiveness in improving access to treatment for those with SMDs. TRANSFORM will develop and test a sustainable intervention that can be integrated into existing clinical care and inform priorities for healthcare providers and policy makers.

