## Aims and objectives of TRANSFORM

The TRANSFORM project aims to improve outcomes of persons with SMDs through better access to effective biomedical care by developing an innovative collaborative care model between traditional/faith healers, mental health professionals, primary care practitioners and community health workers (CHWs). We will develop and test community-delivered identification and referral pathways that recognise and engage with the experiences of mental ill health, existing beliefs about causation and treatment, and pluralistic help-seeking of slum-dwellers in Dhaka (Bangladesh) and Ibadan (Nigeria).

One of the key outputs of our project will be an intervention co-developed with key community stakeholders, which will improve the care of people with SMDs while protecting their human rights and meaningfully engaging with traditional and faith-based healers. Establishing such collaborations is not without particular and context-specific challenges, including long-held beliefs about mental health and illness and the power differentials between traditional healers and biomedical practitioners.^27^ Our innovative, bottom-up approach, whereby intervention and training are co-developed by healers, primary care workers and mental health practitioners in a spirit of mutual respect, seeks to address these challenges and promote participatory inclusiveness from all stakeholders.

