### Work package 4: community identification, referral and outcome assessment of people with SMDs (months 24–48)

Our aim for WP4 is to determine whether our interventions lead to an increase in numbers of people with SMDs accessing biomedical care. We will further ascertain these individuals’ initial and follow-up mental health status and quality of life, reduction in caregiver burden, and changes in community attitudes and help-seeking for SMDs. We will collect data pre-intervention to identify the number of people with SMDs attending mental health services from the study site and their basic clinical and sociodemographic characteristics. Data collection systems will be in place for baseline and follow-up assessments of successive patients identified with signs of SMD and enrolled into the study over 12 months.

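### Change from intake to month 3 in a single post-training cohort cannot show an effect of the training on patients' health status

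*Protocol article*

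**What the plan says.** The project "aims to improve outcomes of persons with SMDs through better access to effective biomedical care" (Aims and objectives). The Quantitative evaluation section then sets out to assess the intervention's impact on the "care pathway of individuals with SMDs and its potential effect on their health status". The primary outcome is not a health measure: "The change in referral rate will be the primary outcome of interest for this study". Health measures are secondary. They are analysed with a linear mixed model for change over time, with patient characteristics, time and the baseline score as covariates. Effect sizes with 95% confidence intervals are to be reported, and the text below Table 1 sets alpha at 0.05 for all analyses.

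The data come from "baseline and follow-up assessments of successive patients identified with signs of SMD and enrolled into the study over 12 months" (Work package 4, months 24–48). The training is delivered in work package 3 (months 18–24), and the Population section says that healers and CHWs identify the participants in work package 4. Before the training, the plan is only to "identify the number of people with SMDs attending mental health services from the study site and their basic clinical and sociodemographic characteristics".

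The carer-burden sentence calls the month 3 assessment post-intervention, as against baseline.

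**The concern.** The intervention is the training of healers and CHWs. Everyone who contributes a GAS, GAF, BMI, EQ-5D, CSRI or PFBS value entered after that training. Nobody who reached care without it is followed on these scales. What the plan estimates is how people change after entering care. What the stated objective asks is whether they fare better because the training took place. These are different quantities, and the first would differ from zero even if the training did nothing for health.

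At stake is the reading of the secondary results. An effect size with a confidence interval that excludes zero, under an objective worded as an effect on health status, invites the conclusion that the training improved symptoms and functioning. Any economic result that took the change in EQ-5D or CSRI as an incremental benefit or cost would carry the same fault.

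**Working it through.** The article states no sample size, SD or effect size for these outcomes, so there is no figure to reproduce. The check has two parts.

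**1. What the schedule can identify (Table 1)**

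| Measure | Pre-intervention | Intake | Months 1, 2 | Month 3 | Post-intervention |
|---|---|---|---|---|---|
| People accessing biomedical care | yes | – | – | – | yes |
| GAS, GAF | – | yes | yes | yes | – |
| BMI, EQ-5D, CSRI, PFBS | – | yes | – | yes | – |

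The only row here with a before-and-after contrast is access to care. For the health scales, exposure to the training takes the same value for every patient at every visit, intake included. A training term would be a constant, inseparable from the intercept. Adjusting for baseline, time and patient characteristics does not change this, because no untrained observation exists to compare with.

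Table 1 keeps month 3 and post-intervention as separate columns, and the PFBS tick falls under month 3. The text's label for that visit therefore does not match the table, and it presents follow-up after intake as a before-and-after contrast of the intervention.

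**2. How large the change could be with no effect of training (illustration; all inputs assumed)**

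Let d be the distance of the cohort's intake mean from the mean of the population it is drawn from, in SD of that population. Let r be the correlation between scores three months apart in that population. Expected improvement from regression to the mean alone is (1 − r) × d.

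- d = 1, r = 0.7: 0.3 × 1 = 0.30 SD
- d = 1, r = 0.5: 0.5 × 1 = 0.50 SD
- d = 0.5, r = 0.7: 0.3 × 0.5 = 0.15 SD
- d = 1.5, r = 0.5: 0.5 × 1.5 = 0.75 SD

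A second form assumes that entrants come from the worst fraction q of a stable normal score. The mean distance is then φ(c)/q with c = Φ⁻¹(q): 0.798, 1.271 and 1.755 for q = 50%, 25% and 10%. Multiplying by (1 − r), with r from 0.8 to 0.4, gives:

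- q = 50%: 0.16 to 0.48 SD
- q = 25%: 0.25 to 0.76 SD
- q = 10%: 0.35 to 1.05 SD

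The chance of a two-sided significant improvement at alpha 0.05 is approximately Φ(shift/SE − 1.96). In the mildest case (q = 50%, r = 0.8) the shift is 0.160 and the SD of change is 0.612. This gives 45% at n = 50, 74% at n = 100 and 96% at n = 200; stronger selection or lower r takes it to nearly 100%. A comparison cohort that entered care in the same way would have the same expected shift. The expected difference would then be zero, and the false-positive rate would return to 5%.

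**3. Consequence for a health-gain ratio, if one were formed**

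If a fraction f of the observed gain would have occurred anyway, cost per unit of gain is understated by a factor of 1/(1 − f): 1.33, 2 and 4 for f = 0.25, 0.5 and 0.75.

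**The case against.** The article is hedged. It speaks of a potential effect, ranks patient outcomes as secondary, describes the model as estimating change over time, labels the work observational and announces a separate SAP. PFBS is already descriptive in Table 1. This softens the claim, but the objective still concerns an effect of the intervention, and GAS, GAF, EQ-5D and CSRI are not marked descriptive. A SAP cannot create follow-up of untrained patients.

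Table 1 also has a clinical characteristics row with pre- and post-intervention ticks, pointing to the assessments listed under it. Those scale rows carry no pre-intervention tick, and the work package 4 text limits earlier data to counts and basic characteristics. At best the row shows who reaches care before and after, not how they fare. The QuIP evaluation addresses attribution, but qualitatively.

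Two stronger readings are tempting and should not be adopted.

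- A reader might infer that the article offers month 3 change as its clinical and cost-effectiveness result. It does not. The abstract's aim is to "implement and evaluate the training packages for clinical and cost-effectiveness in improving access to treatment for those with SMDs", so effectiveness is tied to access, which has its own before-and-after row. Work package 5 asks a general question about costs and benefits and never names EQ-5D or CSRI change as its benefit measure; such detail may sit in a full protocol that is not shown.
- A reader might infer that a significant improvement is all but certain. That needs a sample size and a degree of selection that the documents do not give. The disorders are described as enduring, and CHW screening may find people who are chronically ill and stable, in whom regression to the mean would be smaller.

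**Conclusion.** The point holds as a limit on what the patient-level data can conclude. Intake-to-month-3 change in this cohort cannot support a statement about the training's effect on health status, because natural course, regression to the mean and ordinary clinic treatment cannot be separated from it. The schedule alone shows this; no assumption is needed.

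The direction is probably towards apparent benefit, on the assumption that many people are identified when more unwell than usual. The size cannot be obtained from the documents: 0.15 to 0.75 SD for d of 0.5 to 1.5 and r of 0.5 to 0.7, all assumed. The primary outcome is unaffected. The economic analysis is affected only if it uses EQ-5D or CSRI change as an incremental quantity.

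**What to change.** - In the Quantitative evaluation section and Table 1, state that changes in GAS, GAF, BMI, EQ-5D, CSRI and PFBS from intake to month 3 describe the course of people entering care, and will not be reported or tested as an effect of the training on health status.
- In the carer-burden sentence, drop the post-intervention label for month 3.
- In work package 5, base cost-effectiveness on the incremental cost of training, supervision and referral per additional person accessing care. Table 1 measures access before and after, and this matches the abstract's wording. Report EQ-5D and CSRI changes descriptively.

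This costs wording only and needs no new data. The downside is a weaker claim for the secondary outcomes. If an effect on health status must remain an objective, a pre-training or concurrent comparison cohort followed on the same scales would be needed, which means new data collection.

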#### Dhaka, Bangladesh

In Dhaka, the study will be conducted in the Korail Basti (*basti* meaning slum). Korail is one of the largest slums in Bangladesh, located in the centre of the city, encroaching on parts Dhaka's most affluent neighbourhoods. The area of the slum is claimed to be between 180 and 220 acres.^29^ The majority of Korail's population (estimated to be around 200 000)^30^ subsist below the poverty line and work in low-income jobs. They have limited access to the city's healthcare services and there is little connection with the surrounding major roads.^31^

There is widespread stigma related to mental illness in Bangladesh.^32^ Referrals of patients with SMDs to mental health specialists by primary healthcare providers are near non-existent, as are mental healthcare facilities.^33^ Many people living in the slums use traditional and faith-based healers. There are nine mosques within the Korail Basti, each with imams (Islamic priests) who are the ‘go-to people’ for mental health problems and support. One key religious healing practice is *Kalami* (a healing practice based on verses of the Qur'an). The healing aims to cure problems through communication with *jinn* (spirits), and treatments can also include giving patients *pani-pora* (blessed water) to exorcise the *jinn*.^34^

The National Institute of Mental Health (NIMH) is Bangladesh's leading public institution dedicated to the treatment of mental health problems, along with mental health policy formation, research and training of mental health professionals. The facility is located 7.3 km from the Korail Basti. It serves as one of the cheapest clinical options for the Korail community and employs over 300 personnel to deliver out-patient, in-patient and emergency medical services for child and adult mental disorders. As the largest psychiatric teaching hospital in the country, NIMH provides training in psychiatry, psychology and medicine as well as engaging in research activities and mental health policy formation.

NIMH has a total of 200 in-patient beds; 70% of these are non-fee-paying government-funded beds and the rest are private fee-paying beds. In-patient and out-patient admissions range across all units, including adult psychiatry and community and social psychiatry. In 2019, 58 846 patients were provided with service through the out-patient department.

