### Work package 2: developing training packages for traditional/faith healers and community health workers; raising community awareness (months 12–18)

We will hold workshops with traditional/faith healers and CHWs to co-produce two training packages. The training package for healers will aim to help them identify signs of SMD in individuals who seek their care. We will identify best pathways for them to refer people with signs of SMD to the local primary care centre or to a CHW. The intervention will be designed not to replace faith and traditional healing practices with biomedical care, but rather to serve as a complement to their role.

For CHWs, we will modify the mhGAP intervention and guide^18^ based on local contextual factors identified through WP1 and based on previous work,^35^ including local taxonomies of mental illness and ideas on causation and help-seeking. The CHW training will upskill them to deliver community-based interventions, including screening and early identification of those with SMDs, psychoeducation, promoting medication adherence, referral and navigation to secondary care services, support for carers and community health promotion. It will also include a component pertaining to effectively liaising with traditional/faith healers, particularly for identifying those with SMDs who need additional care.

We will also co-produce media in various formats, such as posters and radio adverts, to engage communities with the intervention. The content and methods used will be informed by findings from WP1.

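### The healer-level primary regression adjusts for patients' characteristics that, on the data described, follow identification, referral or entry to care and have no healer-specific value when a healer makes no referral

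*Protocol article*

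**What the plan says.** The Quantitative evaluation section of the Protocol article states: "The change in referral rate will be the primary outcome of interest for this study". It will be assessed by "comparing referral rates made to the participating healers 12 months before and after intervention (training) is delivered". I read this as referrals made by healers, because the next paragraph of that section follows up what became of a healer's referral. A pre–post regression will then "quantify the referral difference at the healer level after adjusting for healers’ and patients’ characteristics". The section adds: "Both the crude and the adjusted rate change and its corresponding 95% confidence interval will be provided".

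The patient data are described in three places:

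- **Population.** Participants enter WP4 by being identified by healers and community health workers (CHWs).
- **Work package 4.** Before the intervention, data are collected to "identify the number of people with SMDs attending mental health services from the study site and their basic clinical and sociodemographic characteristics". Afterwards the plan is for "baseline and follow-up assessments of successive patients identified with signs of SMD and enrolled into the study over 12 months".
- **Table 1.** For each referral, the CHW records only its date and source. The source may be the person, a family member or a healer, and the row is ticked post-intervention only. Age, gender, religious background, area of residence, number of children and the clinical characteristics of people accessing care are ticked pre-intervention. Education, employment, socioeconomic status, GAS and GAF are ticked only from intake onward.

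Below Table 1, the article leaves the detailed analyses, missing values and model-assumption violations to a SAP.

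**The concern.** The unit of the primary model is the healer, observed for 12 months before and 12 months after training. A patient covariate fits such a model only if it describes patients of that healer in that period. On the data described, this raises three problems.

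1. **Timing.** The patients with data have already been identified, enrolled or admitted to care. Their characteristics are observed after the event that the outcome counts.
2. **Effect of training.** Under Work package 2, healers are trained to recognise signs of SMD, and for the route onward the article says: "We will identify best pathways for them to refer people with signs of SMD". Training may therefore change who is referred. Adjusting for the case-mix of the referred is then adjustment for a consequence of the intervention, not control of confounding.
3. **Existence.** A healer who refers nobody in a period has no referred patients to describe. No true value exists to impute, so a missing-data rule in the SAP would not solve this.

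At stake is the adjusted estimate of the primary outcome. The article does not say whether the crude or the adjusted estimate decides the result.

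**Working it through.** **Step 1: is there a usable source for the covariate?**

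| Needed for a healer-level patient covariate | What the article describes |
|---|---|
| Data on a healer's clients, referred or not | None on non-referred clients |
| Pre-training data linked to a healer | Records of people attending services by any route; no link to a healer stated |
| Post-training data linked to a healer | Intake data on enrolled people; the referral source may also be self or family |
| The same variables in both periods | A few demographic and clinical items pre-intervention; most from intake only |
| A value in every healer-period | Undefined where the healer made no referral |

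**Step 2: how large could the bias be if zero-referral rows are dropped?**

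The article gives no number of healers, referral rate, effect size or power, so there is no planned figure to reproduce. All inputs here are assumptions: a true rate ratio of 2, and a range of pre-training means m per healer per 12 months.

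For Poisson counts, P(0) = e^(−m), and the mean among non-zero periods is m/(1 − e^(−m)). The ratio obtained after dropping zeros is

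[2m/(1 − e^(−2m))] / [m/(1 − e^(−m))].

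Example, m = 1: 2/(1 − 0.135) = 2.31; 1/(1 − 0.368) = 1.58; 2.31/1.58 = 1.46.

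For a negative binomial with dispersion 1, P(0) = 1/(1 + m), the non-zero mean is 1 + m, and the ratio is (1 + 2m)/(1 + m).

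| Mean before → after | Poisson zero share, before / after | Ratio, Poisson | Ratio, negative binomial |
|---|---|---|---|
| 0.25 → 0.5 | 78% / 61% | 1.12 | 1.20 |
| 0.5 → 1 | 61% / 37% | 1.24 | 1.33 |
| 1 → 2 | 37% / 14% | 1.46 | 1.50 |
| 2 → 4 | 14% / 2% | 1.76 | 1.67 |
| 5 → 10 | 0.7% / 0.0% | 1.99 | 1.83 |

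**Step 3: simulation.** There were 20,000 healers per period, with rates varying between healers and a true ratio of 2. Training was assumed to raise the share of milder cases among the referred from 20% to 50%.

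| Pre-training mean | All rows, no patient covariate | Non-zero rows, no covariate | Non-zero rows, adjusted for case-mix | Rows dropped |
|---|---|---|---|---|
| 0.5 | 2.02 | 1.28 | 1.28 | 52% |
| 2 | 1.99 | 1.69 | 1.69 | 13% |

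Keeping every healer-period recovers the assumed ratio. In this set-up the whole attenuation comes from row loss, and the covariate itself added almost nothing. The separate effect of adjusting for a characteristic that training alters is therefore not quantified here, and its direction is not guaranteed.

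**The case against.** Several stronger readings are tempting, and the article does not support them.

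- **That patient data exist only for referred people.** This is too narrow. The pre-intervention records cover everyone with an SMD attending services from the study site, and people may be identified by CHWs or come through self or family referral.
- **That the adjusted model necessarily loses healers with no referrals.** The article does not say this. It follows only if characteristics are summarised per healer and period and incomplete rows are dropped. Site-level case-mix would lose no rows, although it would not be healer-specific and would still come from people identified or already in care. Aggregation and missing values may be settled in a SAP that is not shown.
- **That healers hardly referred before training.** This is plausible, since the project sets up their pathway, but it is not documented. The Dhaka section says referrals "to mental health specialists by primary healthcare providers are near non-existent". That concerns primary care in Bangladesh, not healers, and says nothing about Ibadan, where the Discussion lists an earlier collaborative-care trial with healers.
- **That the primary result as a whole is compromised.** The crude rate change is promised with its interval, does not use these covariates, and would help to reveal attenuation.

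It can also be argued that the article gives no denominator for the rate, and that if the rate were per client seen, the characteristics of clients seen would be ordinary case-mix. That is correct in principle, but no data on clients seen are described.

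These points limit the claim. They do not remove it: the adjustment for patients' characteristics is stated in the article itself, and the data described cannot supply a sound version of it at healer level.

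**Conclusion.** The point holds as a flaw in a stated adjustment. On the data described, patients' characteristics are observed after referral or entry to care, may be changed by the training, have no stated pre-training link to a healer, and are undefined at healer level where no referral was made. The adjusted primary estimate can therefore be biased. The direction is known, toward no change, only for the case where zero-referral healer-periods are dropped.

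The size cannot be computed from the article. The illustration rests on an assumed true ratio of 2, Poisson counts and deletion of zero rows. It gives about 1.1 to 1.5 at pre-training means of 0.25 to 1 per year and almost no bias at 5 per year. With overdispersed counts some bias remains at 5 per year (1.83). The matter is serious if referrals per healer are rare and minor if they are frequent.

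**What to change.** In the Quantitative evaluation section:

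- Remove patients' characteristics from the healer-level model of referral rate.
- Adjust only for healer and site characteristics that are fixed before training and defined for every healer-period.
- State that healer-periods with zero referrals stay in the analysis.
- Describe the case-mix of referred people separately for each period, as a descriptive result.

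The choice of count model can be left to the SAP. The cost is a change of wording in the protocol, carried into the SAP; no additional data are needed.
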